### Intervention

The intervention to be evaluated is a combination of Triple P Discussion Groups and Stress Control. The Triple P-Positive Parenting Program is a public health approach to preventing and treating emotional, behavioural and developmental problems displayed by children and adolescents [18] (http://www.triplep.net). This is achieved through increasing knowledge, skills, and confidence in parenting. Triple P uses a tiered system of intervention with five levels of increasing strength, ranging from information-based strategies delivered via the media (level 1) to intensive individually tailored multi-session programmes (level 5). Four meta-analyses examining the outcomes of Triple P interventions have demonstrated positive effects for child behaviour problems, parenting practices and self-efficacy, and parental wellbeing [19-22].

The Triple P Discussion Groups are a level 3, low-intensity intervention designed to provide specific advice about common child behaviour or developmental issues. The Triple P Discussion Groups are interactive in nature and are typically run with 10–20 parents. Previous research evaluating the Triple P Discussion Groups using randomised controlled trial designs has found that in comparison to a control group, participants in the intervention condition reported significantly fewer child behaviour problems, less dysfunctional/ineffective parenting practices, and greater parenting self-efficacy after attending the programme [23,24].

Two 120 minute Triple P Discussion Groups will be used in this study; the ‘Being a Positive Parent’ and the ‘Dealing with Disobedience’ Triple P Discussion Groups (see Table 2 for information about session content, duration, and delivery). All practitioners delivering the Triple P Discussion Groups will be trained in Triple P and standardised training is provided by Triple P International (for more information on training see: http://www.triplep.net).

Stress Control is a low-intensity cognitive behavioural intervention that aims to promote mental health and wellbeing on a community-wide basis [25] (http://www.glasgowsteps.com). The central focus of Stress Control is to teach cognitive behavioural therapy techniques to help individuals cope with anxiety, depression, panic, poor sleep, and/or low self-confidence. The programme is didactic in nature, consists of six 90 minute group sessions, and is typically delivered to 30–100 people [25] (see Table 2 for information about session content, duration, and delivery). Research evaluating Stress Control using controlled trial designs and pre-post uncontrolled designs has found that Stress Control is effective in reducing participants’ anxiety, depression, and distress, and improves general psychological wellbeing [25-28]. The practitioners delivering the Stress Control sessions are staff from the NHS GGC STEPS Primary Care and Mental Health Team. The STEPS Primary Care and Mental Health Team provide a range of mental health services to individuals in South East Glasgow and Stress Control is delivered as part of their regular practice. All practitioners delivering the Stress Control sessions are trained to deliver the programme. Training and supervision is provided by the programme developer, [name], a member of the STEPS Primary Care and Mental Health Team.

**Table 2 T2:** Overview of intervention sessions

**Session**	**Content**	**Duration**	**Delivered by**
Being a Positive Parent Triple P Discussion Group	• Introduction to principals of positive parenting	120 minutes	Trained Triple P practitioners employed by the NHS GGC
	• Taught skills to support child’s competence and development, and build a positive relationship with their child		
Dealing with Disobedience Triple P Discussion Group	• Introduction to reasons for child disobedience and parenting traps		
	• Taught skills to encourage positive child behaviour and to manage disobedience		
Stress Control Session 1: Information about stress	• Introduction to Stress Control	90 minutes	Employees of the NHS GGC, STEPS Primary Care and Mental Health Team
	• Information about common mental health problems provided		
Stress Control Session 2: Controlling your body	• Introduction to how stress affects your body		
	• Taught skills to control your body		
Stress Control Session 3: Controlling your thoughts	• Introduction to how stress affects your thoughts		
	• Taught skills to control your thoughts		
Stress Control Session 4: Controlling your actions	• Introduction to how stress affects your actions		
	• Taught skills to control your actions		
Stress Control Session 5: Controlling your panic, using your breathing to control stress, prevention skills and medication	• Introduction to panic and stress		
	• Taught skills to control panic		
	• Information on medications and antidepressants is provided		
Stress Control Session 6: Controlling your sleep, wellbeing, and controlling your future	• Introduction to how stress affects your sleep		
	• Introduction to wellbeing		
	• Skills to control your sleep and managing stress in the future		

### Intervention condition

Families allocated to the intervention condition will receive the intervention immediately after the pre-intervention measures. The intervention is delivered over an eight week period with one session per week. The Triple P Discussion Groups are delivered first followed by Stress Control. We assumed that participants would be more likely to drop out towards the end of the intervention and therefore decided that the Triple P Discussion Groups should be delivered first to ensure most participants were exposed to at least some of each intervention. The mid-intervention questionnaire will be administered at the end of the Triple P Discussion Group sessions but prior to the start the Stress Control sessions (i.e., approximately two weeks after the start of the intervention). Post-intervention measures will be administered immediately after the end of the Stress Control sessions, and a follow-up questionnaire approximately 3-months later. The duration of the study for participants in the intervention condition is from referral until the 3-month follow-up questionnaire. For these participants, the approximate length of the time in the study is 24 weeks. Participants allocated to the intervention condition are able to utilise any other service during the duration of the study. This may include services aimed to improve their mental health, their parenting, or their child’s behaviour, and participants will be asked about use of other services.

### Waitlist condition

Families allocated to the waitlist condition will be asked to wait approximately 12 weeks before they participate in the intervention. During the 12 weeks, participants in the waitlist condition will complete questionnaire measures at two time points; at the equivalent times of mid- and post-intervention questionnaires for the intervention group. After the post-intervention equivalent questionnaire has been completed, participants will be offered the intervention. The duration of the study for participants in the waitlist control condition is from referral until the end of the intervention. For these participants, the approximate length of the time in the study is 20 weeks. Like participants in the intervention condition, participants allocated to the waitlist condition are able to utilise any other service during the duration of the study and information about their use of other services will be obtained.

### Measures

A description of the measures used in the study, the time points of administration, and the rational for use is reported in Table 3. As the combined intervention of Triple P Discussion Groups and Stress Control has a dual focus on parenting practices and mental health, there are two primary outcomes of the study: change in dysfunctional/ineffective parenting practices and change in symptoms of depression, anxiety, and stress. Secondary outcome measures assess change in child behaviour, parenting experiences, parental self-efficacy, xfamily relationships, and positive parental mental health. Other measures include family demographics and participant satisfaction with the intervention. For families with two or more parents/carers, only one parent/carer will be asked to complete the outcome measures, although all parents/carers will be encouraged to participate in the intervention. If there is more than one child in the family in the target age range who meets the eligibility criteria, the participant will be asked to choose a target child (the one who is the most cause for concern) to complete the measures about.

Treatment fidelity of the Triple P Discussion Groups and Stress Control sessions will also be measured (see Table 3). The practitioners delivering the sessions will complete a session content checklist after the end of each session and the percentage of content covered will be calculated. In addition, all group sessions will be audio-recorded and approximately 30% of the recorded sessions will be randomly checked by an independent observer. Adherence to the intervention content will be recorded using the same session checklist. Agreement between the practitioner-com-pleted session checklist and the session checklist completed by the independent observer will be examined to determine the extent of inter-observer agreement on treatment fidelity.

**Table 3 T3:** Measures and data collection points

**Construct**	**Measure**	**Administration time point**				**Rationale for use**
		**Pre-**	**Mid-**	**Post-**	**follow-up**	
		**intervention**	**intervention**	**intervention**	**follow-up**	
*Primary outcome measures*						
Dysfunctional/ineffective parenting practices	The Parenting Scale (PS) [29]	✓	✓	✓	✓	To measure the effects of the combined intervention on dysfunctional/ineffective parenting practices
Parent mental health	Depression Anxiety Stress Scales-21 (DASS-21) [30]	✓	✓	✓	✓	To measure the effects of the combined intervention on symptoms of depression, anxiety, and stress
*Secondary outcome measures*						
Disruptive child behaviour	Eyberg Child Behavior Inventory-Intensity Scale (ECBI-I) [31]	✓		✓	✓	To measure the effects of the combined intervention on children’s behaviour
Parenting experiences	Parenting Experience Survey (PES) [32]	✓		✓	✓	To measure the effects of the combined intervention on parenting experiences
Parental self-efficacy	Child Adjustment and Parent Efficacy Scale-Parent Efficacy subscale (CAPES-PE) (Morawska A, Sanders MR, Haslam D, Filus A, Fletcher R: Child Adjustment and Parent Efficacy Scale (CAPES): development and initial validation of a parent report measure, submitted)	✓		✓	✓	To measure the effects of the combined intervention on parental self-efficacy
Family relationships	Parenting and Family Adjustment Scale-Family Relationships subscale (PAFAS-FR) [33]	✓		✓	✓	To measure the effects of the combined intervention on family relationships
Positive parent mental health	Short Warwick-Edinburgh Mental Well-being Scale (SWEMWBS) [34]	✓		✓	✓	To measure the effects of the combined intervention on parental positive mental health
*Other measures*						
Family demographics	Family Background Questionnaire	✓				To describe the demographic information of the participating families
Participant satisfaction with the Triple P Discussion Groups	Triple P Client Satisfaction Questionnaire (CSQ) [35]			✓		To measure the acceptability and satisfaction with the Triple P Discussion Group sessions
Participant satisfaction with Stress Control	Stress Control Client Satisfaction Questionnaire			✓		To measure the acceptability and satisfaction with the Stress Control sessions
		**Procedure**				
Treatment fidelity of Triple P Discussion Groups	Session content checklist [36]	Completed by the practitioner/s at the end of each Triple P Discussion Group				To determine treatment fidelity and integrity of the Triple P Discussion Group sessions
Inter-observer agreement of treatment fidelity of Triple P Discussion Groups	Session content checklist [36]	All Triple P Discussion Group sessions will be audio-recorded and approximately 30% of the recorded sessions will be randomly checked by an independent observer. Adherence to the intervention content will be recorded and inter-observer agreement calculated				To determine inter-observer agreement on the session content checklist designed to determine treatment fidelity of the Triple P Discussion Group sessions
Treatment fidelity of Stress Control	Session content checklist - developed for this study	Completed by the practitioner/s at the end of each Stress Control session				To determine treatment fidelity and integrity of the Stress Control sessions
Inter-observer agreement of treatment fidelity of Stress Control	Session content checklist - developed for this study	All Stress Control sessions will be audio-recorded and approximately 30% of the recorded sessions will be randomly checked by an independent observer. Adherence to the intervention content will be recorded and inter-observer agreement calculated				To determine inter-observer agreement on the session content checklist designed to determine treatment fidelity of the Stress Control sessions

### Data collection procedure

Information from participants will be obtained through questionnaires. Questionnaires will be administered in a variety of ways including during home visits, via the telephone, hardcopy via post, and online, depending on each participant’s preference. Contact with participants will be made via email and phone if questionnaires are not completed and returned.

### Data analysis procedure

Descriptive statistics will be used to present participation and retention rates. Means and standard deviations will be presented for continuous outcome measures and frequencies and percentages will be presented for categorical variables. The pre-intervention characteristics of participants in each condition (intervention and waitlist) will be compared. Chi-squared tests will be used to compare any group differences for categorical variables and *t*-tests will be used for continuous variables. Missing data will be explored following data collection and depending on the amount and type of missing data, a range of methods may be utilised. It is likely that imputation techniques will be used to extrapolate missing data.

Univariate and multivariate analyses will be conducted to examine the effects of the combined intervention in comparison to the waitlist condition on changes in dysfunctional/ineffective parenting practices, parental mental health, children’s behaviour, parenting experiences, parenting self-efficacy, family relationships, and parental positive mental health. All analyses will use an intent-to-treat approach using data from all participants who completed pre-intervention measures. In addition to intent-to-treat analyses, per protocol analyses will be conducted using data from participants who attended at least one session of the intervention and who completed measures at more than one time point. SPSS will be used to conduct the analyses and estimates of effects will be calculated and reported using Cohen’s *d*. Reporting of the trial will follow the CONSORT guidelines.

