## Methods/design

### Design

The study is designed as a feasibility RCT (see Figure 1). First, informed consent will be obtained from all participants, followed by pre-intervention measures being administered. After pre-intervention measures are completed, participants will be randomly assigned to either an intervention or a waitlist condition. The intervention condition receives the combined intervention of Triple P Discussion Groups and Stress Control immediately after pre-intervention measures, whereas, the waitlist condition receives the intervention approximately 12 weeks later. To evaluate the effects of the intervention in comparison to a waitlist, participants in the intervention condition will complete questionnaire measures at mid-intervention and post-intervention. Participants in the waitlist condition will complete the same measures at the equivalent times. Participants allocated to the intervention condition will also complete questionnaire measures at 3-month follow-up. The National Health Service (NHS) West of Scotland Research Ethics Committee (REC ref 12/WS/0242) and the NHS Research and Development Management Office (R&D ref GN12FS463) have approved the study protocol and documentation.

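### The supplementary per-protocol set requires session attendance, a criterion that cannot apply alike in the intervention and waitlist arms

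*Protocol article*

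**What the plan says.** The Data analysis procedure section sets out analyses to "examine the effects of the combined intervention in comparison to the waitlist condition". The main set is intent-to-treat, covering everyone with pre-intervention measures. In addition, "per protocol analyses will be conducted using data from participants who attended at least one session of the intervention" and whose measures were completed at more than one time point. One rule is given for all participants, with no separate criterion for the waitlist arm.

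The Waitlist condition section fixes when that arm can attend: "Families allocated to the waitlist condition will be asked to wait approximately 12 weeks before they participate in the intervention". It adds: "During the 12 weeks, participants in the waitlist condition will complete questionnaire measures at two time points", matching the mid- and post-intervention questionnaires. Then: "After the post-intervention equivalent questionnaire has been completed, participants will be offered the intervention".

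The Design section gives the last assessment to one arm only: "Participants allocated to the intervention condition will also complete questionnaire measures at 3-month follow-up". No such assessment is described for the waitlist arm.

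**The concern.** A per-protocol comparison needs a criterion that has a meaning in each arm before the outcome is measured. Here the criterion is attendance, and the design withholds sessions from the waitlist arm until its last compared outcome is in. Whoever runs the analysis must choose how the rule treats waitlist families, and none of the choices preserves the comparability that randomisation gave.

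What is at stake is the supplementary estimate. Parents who come to at least one session may differ in prognosis from those who never come. The waitlist arm contains both kinds, and they cannot be told apart before the outcome. A difference between attenders and waitlist families then mixes the effect of the programme with the effect of being someone who attends. The article's Discussion says the results could inform a larger trial and possible routine NHS use, so a per-protocol estimate shown beside the intent-to-treat one may be given weight.

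**Working it through.** **1. The timeline.**

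| Time point | Intervention arm | Waitlist arm | Could a waitlist family have attended? |
|---|---|---|---|
| Pre | measured | measured | no |
| Mid | measured after Triple P | measured | no |
| Post | measured after Stress Control | measured | no |
| 3-month follow-up | measured | not measured | no between-arm comparison |

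Every between-arm comparison (mid and post) comes before any waitlist session.

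**2. The possible readings of the rule.**

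- *A. Attendance counted up to the compared outcome.* 0 of 80 waitlist families qualify, so there is no comparator.
- *B. Attendance counted over the whole study.* Waitlist families qualify by attending after about week 12. Inclusion then depends on an event later than their outcome, and possibly influenced by it.
- *C. Attendance applied only to the arm offered sessions.* Attenders are compared with waitlist families not selected on attendance. The second condition (measures at more than one time point) can still be applied in both arms, so the comparator is not every waitlist family.

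**3. The plan's own figures (Sample size section).** PS Total: 0.3 / 0.6 = 0.5 SD. DASS-21 Total: 5 / 10 = 0.5 SD. A two-sided t-test at alpha 0.05 and 80% power needs 63.8, so 64 per arm (the normal approximation gives 63). Then 128 / 0.8 = 160. The stated sample size reproduces and is not in question. It supplies the scale for the bias.

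**4. Size of the bias under reading C.** Assumptions not in the article: a share *a* of intervention families attends at least once; attendance is driven by a standard normal propensity with correlation *r* to the outcome; there is no true effect. Then

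bias (SD units) = *r* × φ(z) / *a*, where z is the standard normal quantile at 1 − *a*.

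For *a* = 0.8: z = −0.842, φ(z) = 0.280, φ(z)/*a* = 0.350.

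| r | Bias (SD) | DASS-21 points (× 10) | PS points (× 0.6) | Share of planned 0.5 SD |
|---|---|---|---|---|
| 0.1 | 0.035 | 0.35 | 0.021 | 7% |
| 0.2 | 0.070 | 0.70 | 0.042 | 14% |
| 0.3 | 0.105 | 1.05 | 0.063 | 21% |

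Varying attendance from 70% to 90% as well, with *r* from 0.1 to 0.3, gives 0.02 to 0.15 SD.

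**5. Type I error under reading C, 80% attendance.** With 64 attenders (0.8 × 80) against 80 waitlist families, SE = √(1/64 + 1/80) = 0.168 SD. The rejection rate is Φ(−1.96 + s) + Φ(−1.96 − s), with s = bias / SE.

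- *r* = 0.1: s = 0.209, giving 0.040 + 0.015 = 5.5%.
- *r* = 0.3: s = 0.626, giving 0.091 + 0.005 = 9.6%.

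Simulation of 20,000 trials per setting, letting the number of attenders vary, gives 5.6% and 8.9%. If the planned 20% attrition is also taken off (about 51 against 64), the formula gives 5.4% and 8.7%.

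**The case against.** The strongest reply is that this is loose wording in a supplementary analysis. For a waitlist family, following protocol means waiting, so an attendance minimum naturally concerns only those offered sessions. Every per-protocol set departs from randomisation to some degree, and the intent-to-treat analysis is kept. Much of this stands: reading C is the most natural, and the main result is untouched. It does not remove the point, because reading C is exactly where selected attenders meet an unselected comparator, and the article fixes the rule itself rather than leaving it open.

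A reader might infer more than the article supports:

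- *That the waitlist arm will in fact be empty.* This follows only from reading A, the least plausible one, since it would make the stated comparison impossible.
- *That one session of eight is the wrong threshold.* Triple P comes first, and the authors write "We assumed that participants would be more likely to drop out towards the end of the intervention", so some families in the set will have seen no Stress Control. But the article does not say that the set is meant to represent receipt of both programmes, and a stricter threshold would select more heavily. This is a preference, not an error.
- *That families with only pre and mid data contribute nothing.* Table 3 collects both primary measures, PS and DASS-21, at mid-intervention. Only the secondary outcomes lack a mid value.
- *That the distortion is known to be large.* Attendance and the correlation are assumptions. The calculation also uses the post score, whereas the article analyses changes. If the attendance driver already shows at baseline, the bias is smaller.

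**Conclusion.** The point holds for the supplementary per-protocol comparison only. As stated, its attendance criterion cannot apply alike in both arms, and no reading of it gives a comparison protected by randomisation. That conclusion rests on the article's own timeline and needs no numerical assumption.

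Its size does need assumptions. Under the most natural reading, with no true effect, 80% attendance and a correlation of 0.1 to 0.3, the spurious difference is about 0.03 to 0.10 SD, up to about one fifth of the planned effect, and the type I error is about 5.5% to 9.5% instead of 5%. The sign follows the sign of the correlation. The intent-to-treat analysis and the sample size are unaffected. The change is worth making, but the trial's main conclusion does not depend on it.

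**What to change.** Replace the between-arm per-protocol comparison with a complier-average causal effect analysis: two-stage least squares with the randomised arm as instrument, keeping all randomised families and treating missing outcomes as in the intent-to-treat analysis. Define exposure as attending at least one session of any kind. Because the waitlist arm is offered no session before the post-intervention questionnaire, non-compliance is one-sided by design, which suits this method. Use number of sessions attended (0 to 8) as a sensitivity analysis, with the linear-dose assumption stated.

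Do not define exposure as at least one session of each programme. Families who attend Triple P only may benefit, on the PS in particular. Coding them as unexposed would breach the exclusion restriction and, if those sessions help, inflate the estimate.

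Show any attenders-only results as exploratory description within the intervention arm, without a contrast to the waitlist.

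The cost is a change of wording. The existing rule already requires attendance to be recorded. The interval is wider: with 80 per arm and 80% attendance, the complier SE is roughly √(2/80) / 0.8 = 0.198 SD, against 0.168 SD for the naive comparison, about 18% larger.
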